#### Randomization

Cluster randomization will be used, choosing day-by-day clusters. For practical reasons, individual randomization is not feasible, so all neonates enrolled in the same day (representing a cluster) will be randomly assigned to the same treatment. This approach randomly assigns daily groups of neonates rather than individual neonates, and neonates within any one day are likely to respond in a similar manner; hence, their data cannot be assumed to be independent. The clustering structure of the data was taken into account in sample size calculation and data analysis planning. A randomization list will be made by an independent statistician using block randomization with block sizes of 4–8. The allocation remains concealed until the actual trial day when the randomization envelope is opened by the surveillance officer on duty at 8 a.m. The midwives are informed at the beginning of each shift of the assigned treatment. The envelopes and assignment cards are discarded after use. The assigned procedure will then be performed until the next randomization. To provide proper PPV to the baby, the American Heart Association and European Resuscitation Council guidelines recommend switching to a supraglottic airway device if the resuscitator considers that the FM is failing [17]. We recommend the resuscitator to optimize the ventilation during 3 mins before considering switching ventilation option from FM to i-gel and vice versa, to keep contamination between arms low.

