### Sample size

Considering our previous phase II trial, we estimate that a reduction of 25% of adverse outcomes may be possible. A sample size of 954 participants (477 per arm) is required to have a 90% chance of detecting, as significant at the 5% level, a decrease in the primary outcome measure from 40% in the standard-of-care arm to 30% in the supraglottic-airway arm. The sample size is increased to 1150 or 1240 because of the day-by-day cluster randomization, assuming an intra-class correlation of 0.10 and an average daily enrollment of three or four participants, respectively.

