### Statistical analysis

A detailed statistical analysis plan—based on the principles in this section—will be developed before the statistical analysis of the trial. Data analysis will be performed by using the statistical software packages Stata, SAS, and R. All tests will be two-sided, and a *P* value of less than 0.05 will be considered statistically significant. Missing data will be considered, and appropriate imputations will be discussed and performed when appropriate. Statistical analysis will include an unadjusted analysis followed by an adjusted analysis. The primary outcome will be compared between the two treatment arms by using the chi-squared test. The secondary outcomes will be compared by using the chi-squared test or Fisher’s test (categorical outcomes) and using the Student’s *t* test or Mann–Whitney test (continuous outcomes). Mixed-effect regression models will be estimated to evaluate the effect of the treatment on binary outcomes, adjusting for clusters (random effect) and clinically relevant confounders. Data analyses will be performed on an intention-to-treat (ITT) basis. However, since the trial is prone to some contamination (i.e., the person resuscitating may decide to shift to the other device) which can be limited by appropriate training but not entirely prevented, a per-protocol analysis and a contamination-adjusted ITT analysis will also be performed. These results will be considered along with the primary ITT analysis when drawing the conclusions of the trial. Subgroup analyses—per treatment center, time of the day (i.e., day/night), and per birth mode—will be carried out with exploratory purpose.

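### Days are randomised in blocks, but the mixed model names only a day effect; if the event rate drifts over time, that model's standard error will be somewhat too wide

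*Protocol article*

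**What the plan says.** The Randomization section makes the day the unit: "Cluster randomization will be used, choosing day-by-day clusters". The allocation list is described as follows: "A randomization list will be made by an independent statistician using block randomization with block sizes of 4–8". An envelope is opened at 8 a.m. on each trial day, and its assignment holds until the next one. The Recruitment and implementation section has babies enrolled every day without a break. A block is therefore a run of about four to eight successive days. The article does not say this in words, but no other reading fits these sections.

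The Sample size section raises 954 babies to 1150 or 1240 for the clustering, "assuming an intra-class correlation of 0.10 and an average daily enrollment of three or four participants, respectively".

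The Statistical analysis section gives two analyses of the primary outcome. The first is unadjusted: "The primary outcome will be compared between the two treatment arms by using the chi-squared test". The second is a mixed-effect regression for binary outcomes, "adjusting for clusters (random effect) and clinically relevant confounders". No block or calendar-period term is named. A detailed analysis plan, built on the principles of that section, "will be developed before the statistical analysis of the trial".

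**The concern.** Each block holds both arms in balance over about a week, so blocks act as time strata. If the underlying event rate moves slowly, through staff turnover or seasonal load for example, the movement shifts both arms alike within a block and largely cancels from the treatment comparison.

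A model with one random effect per day and no block term does not know this. It treats all days as independent draws, puts the slow movement into the day variance, and carries it into the standard error. The interval then comes out wider than the design warrants, and the test runs below its nominal 5%. What is at stake is precision that the blocked allocation has already secured. The validity of the result is not at stake.

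**Working it through.** **Inputs from the protocol article.** Event rates 40% and 30%, two-sided 5%, power 90%, intra-class correlation (ICC) 0.10, m = 3 or 4 babies per day, total N = 1150 or 1240, blocks of 4 to 8 days.

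**Input not in the documents.** f, the share of the day-level ICC that lies between blocks (slow drift). It is assumed here and varied.

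**Step 1: reproduce the plan's sample size.** The two-proportion formula without continuity correction gives 477 per arm, 954 in all, as stated. With the design effect 1 + (m − 1) × 0.10:
- m = 3: 954 × 1.2 = 1144.8 (stated 1150)
- m = 4: 954 × 1.3 = 1240.2 (stated 1240)

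**Step 2: days and blocks.** 1150/3 = 383 days and 1240/4 = 310 days. At 4 to 8 days per block this is between 310/8 ≈ 39 and 383/4 ≈ 96 blocks, enough to estimate a block variance.

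**Step 3: size of the effect by formula.** Per-baby variance, in units of the independent-data variance:
- as the day-only model counts it: 0.90 + m × 0.10
- as the blocked design delivers it: 0.90 + m × 0.10 × (1 − f)

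The standard error is too wide by the factor k, the square root of the first over the second. The true two-sided size of the day-only test is 2(1 − Φ(1.96k)).

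| m | f | k | true size | power, day only | power, with block |
|---|---|---|---|---|---|
| 3 | 0 | 1.00 | 5.0% | 90.4% | 90.4% |
| 3 | 0.25 | √(1.2/1.125) = 1.033 | 4.3% | 91.1% | 92.1% |
| 3 | 0.50 | √(1.2/1.05) = 1.069 | 3.6% | 91.8% | 93.7% |
| 4 | 0 | 1.00 | 5.0% | 90.2% | 90.2% |
| 4 | 0.25 | √(1.3/1.2) = 1.041 | 4.1% | 91.1% | 92.3% |
| 4 | 0.50 | √(1.3/1.1) = 1.087 | 3.3% | 92.0% | 94.3% |

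At the extreme f = 1, where all day-to-day variation is slow drift, k is 1.16 (m = 3) or 1.20 (m = 4).

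Put as sample size for m = 4, the reported interval would be that of a trial of 1240 × 1.2/1.3 ≈ 1145 babies at f = 0.25, or 1240 × 1.1/1.3 ≈ 1049 at f = 0.50.

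**Step 4: simulation.** The formula assumes equal numbers per day and a normal approximation on the risk-difference scale. A simulation with Poisson daily counts, blocks of 4, 6 or 8 days, smooth drift and no treatment effect (1,500 trials per setting) compared weighted day-level regressions with and without block terms. The ratio of the day-only model's standard error to the empirical one was 1.02–1.03 at f = 0.25 and 1.05–1.07 at f = 0.50. At f = 0 it was 0.97–1.00, so no excess width. With block terms, type I error was 4.1–5.3% wherever drift was present.

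**Step 5: the chi-squared test, for contrast.** It uses a variance of 1, so its true size is 2(1 − Φ(1.96/√v)), where v is the blocked-design variance above. This gives 7.4–8.6% at f = 0 and 5.6–6.2% at f = 0.50. It reaches 5% only where v = 1: f = 2/3 for m = 3 and f = 0.75 for m = 4.

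**The case against.** **Deferral to the analysis plan.** The article postpones detail and leaves the adjustment set open, so a block or period term is not ruled out. That is fair, and the omission need not be final. But the later plan is to rest on the principles stated here, and the one structural term stated is the cluster effect. A feature of the allocation list is not naturally a clinical confounder. Naming the block is a concrete improvement on the stated model.

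**Drift is not shown.** This stands. The article describes similarity within a day and gives a day-level ICC; it reports nothing on movement over weeks or months. A reader might infer that the interval will be too wide. The documents support only that it will be if the rate common to both arms drifts.

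**Learning as the cause.** Staff were trained in November 2017 and recruitment began in May 2018, so a learning curve with the new device is a tempting explanation. It would act mainly on the supraglottic-airway days, which makes it partly a treatment-by-time effect. A block intercept cannot fully absorb that.

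**Wrong test.** A reader might also infer that the primary analysis as a whole is conservative. It is not: the chi-squared test named for the primary outcome ignores the days and is usually anti-conservative (step 5). That is a separate and more serious fault.

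**Small harm.** Also fair. Even with blocks ignored, power in the table is at or above the planned 90%.

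**Conclusion.** The point holds, conditionally and for the mixed model only. The design balances arms within short runs of days, and the model as described does not use that. Under common drift the standard error would be about 3–4% too wide if a quarter of the day-level ICC lies between blocks, and 7–9% if half does; simulation puts these at 2–3% and 5–7%. With no drift there is no loss. The shares are assumptions, as is the reading of blocks as successive days. The treatment estimate stays unbiased and the false-positive rate does not rise, so the documents give no ground to call the mixed-model result invalid. Severity is low: this is a free gain in precision.

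**What to change.** In the Statistical analysis section, or in the analysis plan that follows from it:

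- For the primary and the other binary outcomes, fit the mixed model with a random intercept for randomisation block and a random intercept for randomisation day (8 a.m. to 8 a.m.) nested within block.
- Base the primary inference on this model. Done together with the block term, this also deals with the chi-squared test's neglect of days.
- State the fallback in advance: if the block variance is estimated at zero or the model does not converge, use the day-only random effect. With three or four babies a day, a three-level binary model may be unstable, so this rule is needed.
- Calendar month as a fixed effect may serve as an approximate alternative. It is not equivalent, because blocks last four to eight days and month terms leave the variation between blocks within a month in the error.

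The cost is one variance term and one column of block numbers, exported from the independent statistician's list with arm codes masked so that the analyst stays masked as the Masking section requires. No patients, visits or procedures change.

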### Safety

Resuscitations will be continuously monitored by video and observed by the attending midwife or physician and the researcher assistant in order to detect AEs and SAEs. Safety measures will include monitoring of SAEs and detection of unexpected changes in incidence of common neonatal complications. The AEs will be managed by the attending hospital physician/midwife/researcher and followed until resolution or until a stable clinical end-point is reached by the clinician responsible for the care of the recruited patient.

If there is a reasonable suspected causal relationship with the intervention, SAEs will be reported to the Mulago Research and Ethics Committee (MREC) to guarantee the safety of the participants. Any suspected unexpected serious adverse reactions (SUSARs) with or without a reasonably plausible causal relationship with use of the supraglottic airway will also be reported to the MREC.

### Ethical considerations

The protocol was approved by the institutional review board of Mulago National Referral Hospital, Uganda; the Uganda National Council of Science and Technology; the Director General from the Ministry of Health, Uganda (MREC 1168); and the Regional Committee for Medical and Health Research Ethics (REK South East reference number 2017/989) in Norway.

Extensive discussions with clinical experts and members of the ethical board were necessary to solve the problem of obtaining consent without delaying the intervention. A two-tier procedure for consent will be implement in this trial because it involves unexpected care of critically ill newborns. All mothers entering the labor ward irrespective of whether their baby is suspected of filling inclusion criteria will receive brief information of the trial after which oral consent will be sought. Mothers whose infants are found eligible at birth will be approached for full written deferred consent for continuing participation. All information, including informed consent and the material used in the trial, will be translated in English and Luganda in a clearly understandable form. A senior investigator will be available to discuss any additional questions regarding the trial.

### Sustainability and scalability

A simplified neonatal resuscitation program that can reduce neonatal deaths due to perinatal asphyxia is the highest newborn global health research priority beyond 2015 [41]. This trial will try to demonstrate the first phase of scalability of an innovative approach to newborn resuscitation.

The training module for supraglottic airway use can easily be integrated to current neonatal resuscitation programs [33]. The cost-effectiveness of a supraglottic airway in a low-resource setting needs to be assessed. Such an investment can be justified only if there is a substantial difference between the supraglottic airway and FM. We estimate that a 25% reduction in adverse outcomes is a clinically significant difference large enough to have policy implications. A reusable cuffless device is already available but is still cost-prohibitive [29], so it will be crucial to explore how the unit cost can be reduced. A historical parallel could be the substantial drop in the cost of anti-retroviral therapy against HIV over the last decades [42], allowing scale-up of treatment to a level that previously seemed impossible in low-resource settings.

## Discussion

Newborn resuscitation training and simulation-based curriculum show mixed results in relation to their impact on newborn mortality [3, 4] and their effect on neurological morbidity remains unknown [43]. Further improvement of neonatal resuscitation performance is crucial.

This large trial is the first to assess the impact on mortality/morbidity of the use of a supraglottic airway device during neonatal resuscitation. It is powered to 90% and designed to add evidence lacking in this field. To the best of our knowledge, only four RCTs comparing LMA or supraglottic airway to FM ventilation including 636 patients have previously been published [18, 19, 25, 26, 32]. They have focused mainly on vital sign outcomes or successful resuscitation [34]. Safety and long-term outcomes remain important knowledge gaps. This task-shifting intervention involves midwives as they are the frontline health workers in many settings where newborn mortality is high. The burden of disease from intrapartum-related events can be reduced if simple and robust technologies for newborn resuscitation can be identified [44].

The trial will also monitor neonatal outcome data until day 7. We hypothesize that effective ventilation will be easier to perform with the supraglottic airway device and significantly decrease early neonatal mortality and brain damage from neonatal encephalopathy. Results from this large trial will contribute to provide evidence that can help define best practice advice for future guidelines.

### Trial status

The trial started recruiting participants on May 8, 2018.

## Data Availability

Not applicable.

## Abbreviations

AE: Adverse event
CRF: Case report form
ETT: Endotracheal tube
FM: Face mask
HBB: Helping Babies Breathe
IDMC: Independent data monitoring committee
ITT: Intention-to-treat
LMA: Laryngeal mask airway
MREC: Mulago Research and Ethics Committee
NICU: Neonatal intensive care unit
ODK: Open data kit
PPV: Positive pressure ventilation
RCT: Randomized controlled trial
SAE: Serious adverse event
